### Population

The target population for the impact evaluation is women of childbearing age, defined as 16–49 years inclusive, and children aged 0–59 months inclusive, who reside permanently in Kiyawa LGA. Women and children will be considered lost to follow-up if they migrate, are temporarily unavailable, or consent is withdrawn. Children of women who are lost to follow-up, or die during the study period, will still be included if they continue to reside in the same compound and an eligible caregiver can provide consent. The intervention is open to all community members, with no age or gender restrictions.

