### Sample size

The under-five mortality rate in Jigawa was reported as 192/1000 livebirths in 2017 [26], and deaths in the first week of life may reasonably account for 15% of the total under-five deaths. More recently, a participatory radio programme on child health and COVID-19 was delivered across the LGA (June–December 2020) and vaccine coverage has increased (unpublished data), which we assume to have reduced mortality. We therefore used a conservative baseline mortality of 100 deaths amongst children aged 7 days to 59 months per 1000 livebirths. With the following parameters, we will have a minimum detectable effect size of 30% [6]: (a) 380 children per cluster, (b) 80% power, (c) 5% significance, (d) intra-cluster correlation of 0.007 [27] and (e) coefficient of variance of cluster size of 0.74. We assume on average there are three children under-five per compound (i.e. 127 compounds per cluster), and therefore, we will sample 4480 compounds overall to allow for ~ 10% loss to follow-up. The sample size was calculated using Stata’s *-clustersampsi-* command [28]. We will review these assumptions following the baseline survey.

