### Analysis

The primary analysis will be intention-to-treat, comparing under-five mortality between intervention and control clusters over a 12-month period (July 2021–June 2022), using mixed-effects logistic regression, with fixed effects for the trial arm (intervention or control), and random effects to adjust for compound-level clustering and trial cluster. Data from the first 6 months of intervention implementation (January–June 2021) will be considered as a baseline period, before any intervention effect would be expected. Any imbalances in baseline characteristics between arms will be presented to the Trial Steering Committee (TSC), who will advise on whether the primary analysis should be adjusted for these. We will conduct a complete case analysis, where only children with confirmed survival outcomes will be included; a sensitivity analysis using multiple imputation will be done, if outcome data is found to be missing at random.

Secondary analyses, using the same mixed-effects model approach, will explore differences in pneumonia prevalence, coverage of prevent and protect indicators, knowledge and care-seeking between intervention and control clusters (Table 3). Changes in pneumonia prevalence, knowledge and care-seeking between baseline and endline surveys will be described and compared using chi-squared tests.

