## Discussion

This cRCT aims to provide robust impact and cost-effectiveness evidence for whole systems—strengthening intervention to improve child health, with a focus on pneumonia, in a high mortality setting.

Our main design challenge was the power calculation. The most recent mortality estimate for Jigawa is from the 2018 Demographic Health Survey [12]. However, the Jigawa State Government has implemented several child health programmes in recent years, including a community nutrition programme (‘Masaki’) covering 10 communities in Kiyawa LGA, increasing vaccine coverage, and a Health Insurance Scheme. This may be further confounded by the recently launched Basic Healthcare Provision Fund, which applies to both intervention and control clusters during the trial period.

The COVID-19 pandemic introduces further uncertainty in the baseline mortality estimate. Modelled reductions in access to care, vaccination coverage and increased malnutrition due to disrupted global supply chains would halt, or reverse mortality gains [40, 41]. Nigeria went into recession in 2020, which could also negatively affect child health and survival. Conversely, empirical data from high-income settings has demonstrated reductions in acute paediatric respiratory hospitalisations resulting from COVID-19 public health measures [42–44]. Investment in water and sanitation, a focus on handwashing and efforts to strengthen oxygen systems in response to COVID-19 should all improve child survival.

A 30% intervention effect on mortality is reasonable, given previous PLA trials and clinical interventions to improve pneumonia case management [6, 45]. However, we risk being under-powered if under-five mortality has declined more rapidly than we presumed, or we are unable to reliably record death events. Community-reported mortality surveillance poses challenges and can suffer from under-reporting and misclassification of stillbirths and early neonatal deaths [21, 22, 24]. In order to mitigate this concern, we re-designed the study from protocol version 1.0, which relied solely on retrospective death reporting through cross-sectional surveys, to incorporate prospective vital events surveillance. We also used the ethnographic platform to adapt and pilot test survey tools, exploring how child deaths are discussed by communities in this context.

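### Multiple imputation is made conditional on outcomes being shown to be missing at random, which observed data cannot show, and the protocol names no other check on the complete-case result

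*Protocol article*

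**What the plan says.** Three parts of the protocol article bear on this.

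- **Analysis.** The primary handling of missing outcomes is: "We will conduct a complete case analysis, where only children with confirmed survival outcomes will be included". The only missing-data sensitivity analysis named is conditional: "a sensitivity analysis using multiple imputation will be done, if outcome data is found to be missing at random". No criterion is given for that finding, and no alternative is named if it is not made. Trial arm is the only fixed effect specified in the primary model; adjustment for baseline imbalance depends on Trial Steering Committee advice.
- **Population.** Loss is defined by three routes: "Women and children will be considered lost to follow-up if they migrate, are temporarily unavailable, or consent is withdrawn". Children of women who are lost or die stay in if they remain in the compound and an eligible caregiver consents.
- **Sample size.** The allowance for loss is about 10%: "we will sample 4480 compounds overall to allow for ~ 10% loss to follow-up".

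**The concern.** MAR is a statement about outcomes that were not seen: given what was recorded, the chance of being missing does not depend on survival. The trial's data can show that missingness is related to recorded variables, which contradicts missingness completely at random. They cannot show that nothing further depends on survival. A rule that waits for MAR to be found therefore cannot be applied as written.

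The rule also has an awkward consequence. With arm the only fixed effect, the complete-case analysis in general treats lost children as resembling retained children of the same arm, cluster and compound. Imputation with recorded covariates would ask only that they resemble retained children with the same recorded history. If MAR is doubted, the plan sets imputation aside and keeps an analysis that is no better protected, with nothing named to test it.

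At stake is whether the trial can show that its mortality estimate is robust to the children it could not follow. The document gives some reason to ask. Migration is a listed route of loss. Communities know their allocation (Randomisation), so loss could differ by arm. A confirmed death needs a supervisor's verification at a verbal autopsy visit (footnote to Table 3), and the article does not say how a reported but unverified death is handled.

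**Working it through.** **Inputs**

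- Loss to follow-up d: about 10% (Sample size). That it falls equally on both arms, and on children as on compounds, is an assumption.
- Observed risk ratio: 0.70, the effect the trial is sized for; the Sample size section states "we will have a minimum detectable effect size of 30"%.
- Multiplier k: mortality in lost children divided by mortality in retained children of the same arm. The documents give no value, so a range is shown.

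**Step 1. Reproduce the plan's figure on loss.** 380 children / 3 per compound = 126.7, rounded to 127 compounds per cluster. 127 × 32 clusters = 4064 compounds. Inflated for loss: 4064 × 1.10 = 4470, or 4064 / 0.90 = 4516; 140 × 32 = 4480 exactly. The stated 4480 implies 1 − 4064/4480 = 9.3% loss, so it agrees with an allowance of about 10%.

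**Step 2. Excess mortality only among lost intervention children.** True risk in an arm = retained risk × [(1 − d) + d × k]. With k = 1 in the control arm:

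RR = 0.70 × [(1 − d) + d × k]

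At d = 0.10:

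- k = 1: 0.70 × 1.0 = 0.70
- k = 2: 0.70 × 1.1 = 0.77
- k = 3: 0.70 × 1.2 = 0.84

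RR = 1 when 0.9 + 0.1k = 1/0.70 = 1.4286, so k = 5.3.

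**Step 3. Same multiplier in both arms.** The bracket appears in numerator and denominator and cancels: 0.70 × 1.1/1.1 = 0.70, and 0.70 × 1.2/1.2 = 0.70. With equal loss, only a difference between arms moves the ratio.

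**Step 4. Range of loss, intervention arm only**

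| Missing in each arm | RR at k = 2 | RR at k = 3 | k at which RR = 1 |
|---|---|---|---|
| 5% | 0.735 | 0.77 | 9.6 |
| 10% | 0.77 | 0.84 | 5.3 |
| 15% | 0.805 | 0.91 | 3.9 |
| 20% | 0.84 | 0.98 | 3.1 |

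**Step 5. Rough check on significance.** Take the stated 80% power for a 30% reduction at face value, with a two-sided 5% test assumed. The implied standard error of the log risk ratio is |ln 0.70| / (1.96 + 0.84) = 0.357/2.80 = 0.127. Holding it fixed, z = 2.80 at k = 1, about 2.05 at k = 2 and about 1.37 at k = 3. For an estimate exactly at the design effect and d = 0.10, significance goes at k of about 2.1.

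Steps 2 to 4 need no absolute mortality level. They use risk ratios, whereas the planned model gives odds ratios, so they indicate scale only.

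**The case against.** **Declining to impute under a doubted MAR assumption is defensible.** This is right as far as it goes. A reader might infer that the plan drops its sensitivity analysis exactly when it is needed. The text does not support that for imputation itself: if loss depends on death, imputation under MAR is biased too and would not expose the problem. What stands is that the condition cannot be verified and that nothing named takes imputation's place.

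**A departure-from-MAR analysis may sit in the statistical analysis plan.** It may, and its absence from an article is not the finding. The finding is the rule the article states, which an analysis plan that follows it would inherit.

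**There is a workable reading: impute if missingness relates to recorded variables.** That can be tested, and the surveys record many such variables. But it tests for departure from missingness completely at random, and it leaves MNAR unexamined.

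**The illustration is one-sided.** It is, as Step 3 shows. Nothing in the documents says that lost intervention children die more often than lost control children.

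**Follow-up is designed to limit loss.** Compounds are geolocated, visits are four-monthly, and children of lost or deceased mothers can remain in the cohort. The 10% is a sampling allowance, not a forecast of missing child outcomes.

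**Two further inferences should be resisted.** One is that missing children would outnumber deaths several times over. That needs an annual risk the protocol does not give; its planning figure is a "conservative baseline mortality of 100 deaths amongst children aged 7 days to 59 months per 1000 livebirths". The other is that undisclosed deaths make the case. The Discussion does say that "Community-reported mortality surveillance poses challenges and can suffer from under-reporting and misclassification of stillbirths and early neonatal deaths", but a concealed death is mainly misclassification, which imputation does not address, and first-week deaths are outside the primary outcome.

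**Conclusion.** The point holds as a defect in a stated rule. The condition on multiple imputation cannot be verified from data, and if MAR is doubted the protocol names no sensitivity analysis to the complete-case result. Removing the condition would cure the first fault but would not protect against loss related to death.

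The possible size is moderate and depends on differential loss. With 10% missing per arm and an observed ratio of 0.70, a doubling or tripling of mortality confined to lost intervention children moves the ratio to 0.77 or 0.84, and the effect vanishes only at about 5.3 times. A common multiplier leaves it unchanged. A result exactly at the design effect could lose significance at a multiplier of about 2.1, if the stated power is right. These are assumed scenarios. The documents do not support a claim that the primary result will be biased, only that its robustness would not be shown under the plan as written. The change should be made, but the primary analysis does not fail without it.

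**What to change.** In the Analysis section, or in the statistical analysis plan with a matching amendment:

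1. Delete the condition. Keep complete case as the primary analysis and always run multiple imputation under MAR as a sensitivity analysis, using recorded baseline covariates and respecting compound and cluster.
2. Add a delta-adjusted or tipping-point analysis in which mortality among children lost to follow-up may differ from that among retained children, separately by arm. Fix the range of multipliers before unblinding; 1 to 5 would nearly reach the tipping point of 5.3 found above for 10% loss.
3. Report the tipping point beside the primary result, with the amount of and reasons for missing outcomes by arm.

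This needs one or two sentences of text and a little more analysis work, with no new data, visits or sample.

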### Design

This is a pragmatic community-based cRCT, following a formative phase of intervention development, concept testing and community engagement. Impact against the primary outcome will be evaluated using an open prospective cohort, recording vital events (pregnancies, births and under-five child deaths) amongst a random sample of women on a rolling 4-monthly basis. Secondary outcomes will be recorded during cross-sectional surveys conducted at baseline (January–March 2021) and end line (July–September 2022) (Fig. 1). The same random sample of compounds, and all eligible women and children residing in these compounds, will be included in both surveys and prospective cohort.

Clusters are defined as the geographical catchment area of the 33 government primary care facilities. Clusters range in population size from approximately 1680 to 24,200 (median 5840). All villages in Kiyawa LGA will be included in the study (*n* = 425 enumerated villages); however, the Kiyawa PHC cluster will be excluded from the impact evaluation as this facility is in a peri-urban area and provides a level of inpatient care—unlike the other primary facilities. Villages are made up of compounds, which are defined as the group of structures (including ‘households’) where extended families live and have shared resources.

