**Secondary outcomes**	
Suspected pneumonia mortality rate	The number of confirmed* deaths classified by InterVA-5 as primarily attributable to acute respiratory infections amongst children aged 7 days–59 months, per 1000 livebirths reported by women in the cohort, in the last 12 months [21]
Pneumonia point prevalence	The proportion of children clinically assessed on the day of the survey who meet 2014 WHO IMCI definition for pneumonia or severe pneumonia, including hypoxemia [22, 46]
Women’s wellbeing	The mean Short Warwick-Edinburgh Mental Wellbeing Scale score amongst women aged 16–49 years [23]
*Treat*	
Knowledge of pneumonia	The proportion of women aged 16–49 who can name both fast and difficulty breathing as signs of pneumonia
Care-seeking for childhood illnesses	The proportion of caregivers who self-reported visiting a formal healthcare provider (including primary, secondary, private or government facilities) within 48 h of illness recognition, amongst those who reported their child has been sick in the previous 2 weeks
*Protect*	
Exclusive breastfeeding	The proportion of children aged 0–6 months whose caregiver self-reports exclusively breastfeeding
Vitamin A	The proportion of children aged 18–59 months with 2 doses of vitamin A
*Prevent*	
Vaccine coverage	The proportion of children aged 18–59 months with complete vaccine coverage according to the Nigerian Childhood Vaccination programme [24]**
Handwashing with soap	The proportion of households who self-report access to soap and water in their home for handwashing
Household air pollution	The proportion of households who self-report cooking indoors with wood/charcoal or dried grass

*Deaths which are verified by a field supervisor during a verbal autopsy visit

**Includes 1 dose BCG, 4 doses oral polio vaccine, 2 doses rotavirus vaccine, 3 doses DPT-Penta, 3 doses PCV-10 and 2 doses measles

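### The chi-squared tests of baseline-to-endline change in pneumonia prevalence and care-seeking cannot separate intervention effect from season or other shared changes (minor; the between-arm analyses are unaffected)

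*Protocol article*

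**What the plan says.** The Design section of the protocol article fixes the timing: "Secondary outcomes will be recorded during cross-sectional surveys conducted at baseline (January–March 2021) and end line (July–September 2022"). The same compounds are visited at both rounds: "The same random sample of compounds, and all eligible women and children residing in these compounds, will be included in both surveys".

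Table 3 defines the two outcomes at issue over very short windows. Pneumonia point prevalence is "The proportion of children clinically assessed on the day of the survey who meet 2014 WHO IMCI definition for pneumonia" or severe pneumonia. Care-seeking is a proportion of caregivers, "amongst those who reported their child has been sick in the previous 2 weeks".

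The Analysis section then plans two things for these outcomes. The first is a comparison of the randomised arms: "Secondary analyses, using the same mixed-effects model approach, will explore differences in pneumonia prevalence, coverage of prevent and protect indicators, knowledge and care-seeking". The second, in the next sentence, is a test of change over time: "Changes in pneumonia prevalence, knowledge and care-seeking between baseline and endline surveys will be described and compared", with chi-squared tests as the method. For this second analysis the article states no arm contrast, no seasonal term and no limit on interpretation. It also does not say whether the test is run within each arm or on both arms pooled.

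**The concern.** A same-day prevalence and a two-week recall outcome describe the weeks in which the survey was done. When two rounds share no month of the year, survey round and calendar season are completely aliased, and no choice of test or standard error can pull them apart.

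Season is not the only shared change. The Control section gives all clusters a child health radio programme throughout the project. The Discussion names the Basic Healthcare Provision Fund, which applies to both arms during the trial, and the uncertain effects of COVID-19.

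A small before-after p-value could thus arise with no intervention effect, and a real improvement could be masked. What is at stake is the reading of a supplementary analysis of secondary outcomes: a significant change between surveys is easily taken as programme impact.

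**Working it through.** The plan gives no figure of its own on this point, so there is none to reproduce. The aliasing follows from the dates; the arithmetic only shows how small a shift the planned test would flag.

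**Inputs from the protocol**
- Survey months: January–March 2021 and July–September 2022 (Design). Shared months: none.
- Survey size: 4480 compounds, 3 under-fives each, about 10% loss (Sample size). 4480 × 3 × 0.90 = 12,096, rounded to 12,000 below. This is an upper figure, because only children present at the visit are screened (Baseline and endline surveys).
- Intra-cluster correlation 0.007 and coefficient of variation of cluster size 0.74 (Sample size). They were set for the mortality calculation and are borrowed here only to bound the illustration.

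**Assumptions, not in the documents**
- Pneumonia prevalence 2%, 5% or 10%.
- Endline-to-baseline seasonal ratio of 1.1 to 1.3, or a 25% fall, with no intervention effect.

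**Step 1. Smallest shift reaching p < 0.05 in a plain chi-squared test.** 1.96 × √(2p(1−p)/12,000):
- p = 0.02: 1.96 × √(0.0392/12,000) = 0.35 percentage points
- p = 0.05: 1.96 × √(0.095/12,000) = 0.55 points
- p = 0.10: 1.96 × √(0.18/12,000) = 0.76 points

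**Step 2. A 25% relative seasonal fall, no intervention effect.** z = 0.25p / √(2q(1−q)/12,000), where q = 0.875p is the pooled proportion. This gives z of about 3.0, 4.7 and 6.9 at 2%, 5% and 10%.

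**Step 3. Allowing for clustering.** With 12,096/32 = 378 children per cluster, the design effect is 1 + ((0.74² + 1) × 378 − 1) × 0.007 = 5.09, and √5.09 = 2.26. The shifts in step 1 become about 0.8, 1.2 and 1.7 points, and the z values in step 2 about 1.3, 2.1 and 3.0. The design effect is treated as an upper bound. The planned chi-squared test, as described, does not apply it.

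**Step 4. Chance of a significant result from season alone** (two-sided 5%, normal approximation for two proportions):

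| Setting | 2% | 5% | 10% |
|---|---|---|---|
| Both arms, 12,096 per survey, ratio 1.1 | 0.19 | 0.41 | 0.72 |
| Both arms, ratio 1.2 | 0.56 | 0.93 | 1.00 |
| Both arms, ratio 1.3 | 0.88 | 1.00 | 1.00 |
| One arm, 6,048 per survey, ratio 1.3 | 0.60 | 0.94 | 1.00 |
| Both arms, ratio 1.3, design effect 5.09 | 0.28 | 0.60 | 0.90 |

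**Step 5. What each contrast recovers.** Take 5% at baseline, a seasonal ratio of 1.3 and a true 20% reduction. Control at endline is 5% × 1.3 = 6.5% (+30%). Intervention is 6.5% × 0.8 = 5.2% (+4%). Pooled it is 5.85% (+17%). The before-after change shows a rise in every case, although the intervention works. The between-arm ratio at endline is 5.2/6.5 = 0.80, the true effect. With no effect both arms rise by 30% and the ratio is 1.00.

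None of these figures applies to care-seeking. Its denominator is limited to caregivers of recently sick children, and the documents do not give its size.

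**The case against.** The strongest reply is that the protocol does not rely on the before-after test to show an effect. The sentence just before it compares the same outcomes between intervention and control clusters with mixed-effects models, and both arms are surveyed in the same calendar window. A reader might infer from the survey dates that the trial cannot show what it achieved on pneumonia or care-seeking. The documents do not support that: a seasonal shift common to both arms cancels in the arm contrast, and nowhere is the before-after change attributed to the intervention. This part of the reply stands and sets the severity.

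If the test is run within each arm, the control-arm change would sit beside the intervention-arm change and could reveal a shared shift. That helps a careful reader, but each p-value would remain uninterpretable as evidence of effect.

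The size and direction of seasonal variation are nowhere in the documents, so the figures above show sensitivity, not an estimated bias. Care-seeking is also conditional on illness, so a seasonal change in how many children are sick does not by itself move that proportion. Both limits stand. They restrict the magnitude, not the aliasing.

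A reader might go further and infer that the arm comparison is itself biased, because each survey takes three months and the article does not say how cluster visits are ordered. That is not supported. Visit order and survey-month covariates commonly belong in a full protocol, field manual or analysis plan, and nothing suggests that one arm is reached earlier. According to the Randomisation section, data collectors are not told which villages are in which arm.

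Knowledge of pneumonia is tested in the same sentence, but it is less plausibly seasonal and is not part of this point.

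**Conclusion.** The point holds in limited form and is minor. As stated, the baseline-to-endline chi-squared tests of pneumonia prevalence and care-seeking compare non-overlapping parts of the year on outcomes tied to the survey day or the preceding fortnight. They cannot separate intervention effect from season or from the other changes common to both arms. That conclusion rests on the protocol's own dates and definitions and needs no assumption about the size of seasonality.

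The illustration does rest on assumptions: the prevalence, the seasonal ratio, and about 12,000 children as a ceiling. Within them, a season-only shift of well under one percentage point would be declared significant by a plain test, or one of roughly 0.8 to 1.7 points under a design effect of about 5. The primary mortality analysis, which compares arms over July 2021–June 2022, and the planned between-arm analysis of the secondary outcomes do not depend on this test.

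**What to change.** Remove the baseline-versus-endline chi-squared tests for pneumonia prevalence and care-seeking. In their place:

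- Report the level at each survey by arm, as description only, with a statement that the two surveys fall in different seasons and that other changes affected both arms.
- Draw inference only from the concurrent intervention-versus-control contrast: either the endline comparison by arm already planned, or an arm-by-survey term added to the planned mixed-effects model with its cluster and compound random effects.

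The change is to wording and model specification. It needs no new data and no change to fieldwork. The cost is the loss of the before-after p-values, which could not be read as evidence of effect in any case.

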**Methods:**

This is a cluster randomised controlled trial, with integrated process and economic evaluations, conducted from January 2021 to September 2022. The trial will be conducted in Kiyawa Local Government Area, Jigawa State, Nigeria, with an estimated population of 230,000. Clusters are defined as primary government health facility catchment areas (*n* = 33). The 33 clusters will be randomly allocated (1:1) in a public ceremony, and 32 clusters included in the impact evaluation.

The trial will evaluate a locally adapted ‘whole systems strengthening’ package of three evidence-based methods: community men’s and women’s groups, Partnership Defined Quality Scorecard and healthcare worker training, mentorship and provision of basic essential equipment and commodities. The primary outcome is mortality of children aged 7 days to 59 months. Mortality will be recorded prospectively using a cohort design, and secondary outcomes measured through baseline and endline cross-sectional surveys.

Assuming the following, we will have a minimum detectable effect size of 30%: (a) baseline mortality of 100 per 1000 livebirths, (b) 4480 compounds with 3 eligible children per compound, (c) 80% power, (d) 5% significance, (e) intra-cluster correlation of 0.007 and (f) coefficient of variance of cluster size of 0.74. Analysis will be by intention-to-treat, comparing intervention and control clusters, adjusting for compound and trial clustering.

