### Randomisation

The 33 clusters will be randomised using a 1:1 ratio between intervention and control. Randomisation will be done publicly, with representatives from the LGA and all the wards, following community consent for the study and the randomisation process. The names of the health facility clusters will be written on pieces of paper, folded and placed in a container by study staff. A community representative will then pull the folded pieces of paper out of the container one by one, in front of community witnesses. The first 17 will be assigned to the intervention, and the final 16 will be assigned to control. Due to the nature of the intervention, communities will not be blinded to their status; however, we will not inform data collectors of the intervention status of villages or that they work across intervention and control clusters, and investigators will be blinded during primary analysis.

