### Sampling

During the formative phase, we conducted a community mapping exercise to create a sampling frame, enumerating all villages and the total number of compounds. We will sample proportionately to cluster size, with a minimum of 50 compounds per cluster. Simple random sampling will be used to generate a list of compound numbers within each cluster. During the baseline survey, data collectors will use an Expanded Programme of Immunization approach [25] to number all the compounds in a village, following these steps: (1) locating the centre of the village with support from a community gate keeper, (2) spinning a pen and walking in the direction it points, (3) numbering the first compound encountered as 1 and (4) walking in a clockwise direction until all compounds are numbered. They will then recruit the compounds according to the generated random sample. The same compounds will be included in all subsequent surveys, and GPS coordinates will be taken to facilitate follow-ups. All eligible women, and children under-five years of age who are under their direct care, residing within sampled compounds will be recruited.

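### Chi-squared tests of baseline-to-endline change ignore clustering and the re-survey of the same compounds, so the change p-values are unreliable in either direction

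*Protocol article*

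**What the plan says.** The Analysis section gives the secondary outcomes two treatments.

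- First, a comparison between arms: "Secondary analyses, using the same mixed-effects model approach, will explore differences in pneumonia prevalence", along with knowledge, care-seeking and the prevent and protect indicators. The approach it refers to is the primary model, which has a fixed effect for arm and random effects for compound and trial cluster.
- Then, a comparison over time: "Changes in pneumonia prevalence, knowledge and care-seeking between baseline and endline surveys will be described and compared using chi-squared tests". No adjustment for clustering, no pairing and no contrast between arms is named for it.

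On who is surveyed, the Design section says "The same random sample of compounds, and all eligible women and children residing in these compounds, will be included in both surveys and prospective cohort", and the Sampling section adds "The same compounds will be included in all subsequent surveys". Baseline is January–March 2021 and endline July–September 2022, about 18 months apart. The abstract gives "32 clusters included in the impact evaluation".

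**The concern.** The data behind the change test are dependent in two ways that a chi-squared test does not see.

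- **Clustering.** Respondents in one catchment resemble each other, and catchments may drift differently between rounds. This cluster-by-round variation adds to the variance of the before-after difference, so the test rejects too often.
- **Repeat measurement.** Compounds are the same in both rounds and many women will be too. Positive correlation between a respondent's two answers reduces the variance of the difference, so the test rejects too rarely.

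The plan recognises the dependence in the sentence just before, where the same outcomes get compound and cluster random effects, and then drops it. At stake are the reported p-values for change in pneumonia prevalence, knowledge and care-seeking.

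**Working it through.** The protocol states no figure for this test, so there is none to reproduce. The check asks what type I error a nominal 5% chi-squared test would have under the protocol's own design inputs.

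**Inputs from the Sample size section:** mean m = 380 children per cluster; CV of cluster size 0.74; ICC ρ = 0.007. That ICC is the mortality input and is borrowed here for the survey outcomes.

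**Assumptions (the protocol gives none of these):** cluster autocorrelation r between rounds, 0 to 1; within-person correlation r_p, either none beyond the cluster or 0.4 with every respondent seen twice; for care-seeking, 10–30% of children sick in the previous two weeks. Extra correlation within compounds is left out.

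**Formula.** Variance of the before-after difference relative to what the chi-squared test assumes:

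V = 1 + [m(1 + CV²) − 1] · ρ(1 − r) − (r_p − ρr)

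The last bracket is zero when there is no person correlation beyond the cluster. Actual type I error = 2 · [1 − Φ(1.96/√V)].

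1 + CV² = 1.5476, so m(1 + CV²) − 1 = 588.09 − 1 = 587.09.

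Worked case, r = 0.8 and no person correlation: V = 1 + 587.09 × 0.007 × 0.2 = 1.82; 1.96/√1.82 = 1.45; type I error 0.146.

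| r | r_p | V | Type I error, formula | Type I error, simulated |
|---|---|---|---|---|
| 0 | none | 5.11 | 0.386 | 0.38 |
| 0.5 | none | 3.05 | 0.262 | 0.25 |
| 0.8 | none | 1.82 | 0.146 | 0.14 |
| 0.8 | 0.4 | 1.43 | 0.101 | 0.10 |
| 1 | none | 1.00 | 0.050 | 0.04–0.05 |
| 1 | 0.4 | 0.61 | 0.012 | 0.01 |

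The simulation used 32 clusters of unequal size, prevalence 0.10 and no true change. Repeating it with 16 clusters, as for a test within one arm, gave nearly the same rates: V depends on cluster size, not on the number of clusters. In the five scenarios where it was also run (all but r = 0.5), a t-test on the 32 cluster-level changes held 4.1–4.9%, and a t-test between arms on those changes held 4.4–5.0%.

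**Care-seeking.** Only recently ill children count, so m = 0.10 × 380 = 38 to 0.30 × 380 = 114. With no person correlation:

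- m = 38: r = 0.5 gives V = 1.20 (7.4%); r = 0.9 gives V = 1.04 (5.5%).
- m = 114: r = 0.5 gives V = 1.61 (12.3%); r = 0.9 gives V = 1.12 (6.4%).

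**Sensitivity to the ICC.** With an assumed ICC of 0.05, 140 respondents per cluster, r = 0.8 and r_p = 0.4, the simulated type I error is about 20%.

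**The case against.** The strongest reply is that the randomised comparison does not rest on this test. The preceding sentence of the Analysis section compares the same outcomes between arms with cluster and compound random effects, and in a randomised trial that difference is a valid effect estimate without a change-from-baseline contrast. This stands, and it limits the point to the supplementary change p-values.

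Three further objections also stand in part.

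- **Size.** The ICC was chosen for mortality, and 380 per cluster does not fit all three outcomes: knowledge is measured in women, care-seeking only in recently ill children, and pneumonia only in children present at the visit. The figures show a plausible range, not an estimate.
- **Overlap.** Compounds are fixed, but membership is open over about 18 months and children age in and out. Overlap of women and children is partial, so a person correlation of 0.4 with full overlap is an extreme.
- **Wording.** The article does not say whether the test is pooled or within arm, or design-adjusted. No adjusted or paired version is named, however, and the plain reading is a standard chi-squared test.

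A reader might infer two stronger things. One is that the p-values are always too small; the table shows that they can equally be too large. The other is that before-after changes will be presented as intervention effects, given the radio programme in all clusters and survey rounds at different times of year. The text promises only to describe and compare change and makes no causal claim from it, so the documents do not support that charge.

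**Conclusion.** The concern holds in limited form. The named test does not match the design, and its p-values for change cannot be relied on in either direction. With ICC 0.007, CV 0.74 and 380 per cluster, actual type I error at a nominal 5% runs from about 1% (cluster effects fully stable, person correlation 0.4) to about 38% (cluster effects independent between rounds). For care-seeking it is about 5–12% under the stated assumptions. The range rests on a borrowed ICC and on assumed autocorrelation and person correlation. That the test omits the dependence does not rest on them; it follows from the Design, Sampling and Analysis sections. The primary mortality analysis and the cluster-adjusted comparison of secondary outcomes between arms are unaffected. This should be fixed, but it does not threaten the trial's main conclusions.

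**What to change.** Delete the chi-squared tests and choose one of two replacements.

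1. **Descriptive.** Report change by arm with cluster-adjusted confidence intervals and no p-values. This is the lighter option and removes the flaw.
2. **Modelled.** Extend the planned mixed-effects model to both survey rounds, with arm, round and arm-by-round terms and random effects for cluster, cluster-by-round and compound, plus woman where she is measured twice and the model fits. Report the arm-by-round contrast as the change result.

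The cost is revised wording and a little programming; no new data are needed. The fuller model may fail to converge for sparse care-seeking data. An analysis of cluster-level changes can then be used, which held close to 5% in the simulations above.
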